#### Strategies to improve adherence to interventions {11c}

As the intervention includes one clinical treatment procedure, no specific strategies exist to improve intervention adherence. However, routine outcome measures from the PRESENT cohort will be used for effect estimation. To minimize missing outcomes on the primary endpoint, a member of the research team will call patients who do not return a questionnaire within 1 week to request the patient to complete the questionnaire and to ask out their response on the primary outcome.

#### Relevant concomitant care permitted or prohibited during the trial {11d}

No concomitant care, interventions, and medications will be prohibited during the trial.

#### Provisions for post-trial care {30}

There are no provisions for post-trial care because we do not expect study related (serious) AEs beyond the risk of unrelated (S)AEs due to the natural course of the disease and (S)AEs related to standard of care. A previous first-in-man study including 13 patients demonstrated that the delivery of SBRT followed by surgical stabilization with or without decompression within 24 h is safe and feasible, and no wound complications were observed within 90 days following treatment [13].

#### Outcomes {12}

The primary outcome is difference in physical functioning four weeks after the start of the treatment (i.e., surgery or radiotherapy) between the intervention and control arm, which will be measured with the European Organization for Research and Treatment of Cancer (EORTC) Quality of Life Questionnaire (QLQ) Core 15 Palliative Care (C15-PAL) [14].

Secondary outcomes include the following:Pain response at 2, 4, 6, and 8 weeks and 3 monthsDuration of pain relief as measured by the Brief Pain Inventory (BPI) [15, 16]Change in HRQOL as measured by the EORTC QLQ-C15-PAL and EORTC QLQ Bone Metastases 22 (BM22) from baseline to 4 and 8 weeks and 3 and 6 months [14, 17, 18]. For the present study, we will focus on overall QOL and the two functional scales (physical and emotional functioning) of the EORTC QLQ-C15-PAL, and the functional interference and psychosocial aspects domains of the EORTC QLQ-BM22 [17, 18]Duration of the hospital stay in daysDays until return to systemic oncological therapy, including hormonal, immune, targeted, and chemotherapyOccurrence of neurological deterioration, defined as deterioration of more than one grade on the American Spinal Cord Injury Association (ASIA) scale as measured by physical examination by a neurologists or trained ASIA physician [19, 20]Local control according to routine imaging and the electronic patient chartAEs, defined as any undesirable experience occurring to a patient during the study that may be related to the experimental treatment procedureProgression-free survival and overall survivalResource use, such as doctor visits, medication, hospital admissions, and surgical interventions, as well as out-of-pocket expenses such as for over-the-counter drugs and travel costs, will be recorded using the iMTA Medical Consumption Questionnaire (iMCQ) at 3 and 6 months [21]Cost-effectiveness

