### Objectives {7}

The primary objective of this study is to evaluate the effectiveness of SBRT followed by surgical stabilization with or without decompression within 24 h compared with the standard of care, which is surgical stabilization with or without decompression followed by radiotherapy (either cRT or SBRT) as soon as the wound is healed sufficiently, in terms of physical functioning at four weeks after the start of the treatment.

Secondary objectives are as follows:To compare the pain response, duration of pain relief, length of hospital stay, time to return to systemic oncological therapy including hormonal, immune, targeted, and chemotherapy, neurological deterioration, adverse events (AEs) such as wound complications, HRQOL, and survival between the intervention and control group, andTo study the cost-effectiveness to assess whether same-day SBRT and surgery is cost-effective compared with the standard of care, from a societal perspective.

It is hypothesized that the same-day treatment procedure will result in faster recovery of mobility, less hospital visits, earlier pain relief from irradiation, and faster restart of systemic oncological therapy without an increase in wound complications due to the short interval between surgery and radiotherapy.

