### Eligibility criteria {10}

To be eligible, patients must meet the following inclusion criteria: (1) at least 18 years of age, (2) having symptomatic (cervical, thoracic and/or lumbar) spinal metastases from solid tumors and (impending) spinal instability requiring surgical stabilization (with or without decompression) and radiotherapy, (3) histologic proof of malignancy or radiographic/clinical characteristics indicating malignancy beyond reasonable doubt, (4) radiographic evidence of spinal metastases, (5) fit for (radio)surgery, (6) participation in PRESENT cohort, including consent for providing PROMs and randomization into future trials, and (7) written informed consent. Potential patients will be excluded when (1) SBRT cannot be delivered, (2) routine surgical stabilization with or without decompression and/or radiotherapy cannot be performed (e.g., multiple spinal metastases requiring surgical bridging of more than five vertebral levels and/or requiring radiotherapy on more than one location), (3) prior surgery or radiotherapy to the index level(s), (4) multiple myeloma, (5) neurological deficits (American Spinal Injury Association (ASIA) impairment scale grade A, B, or C) or partial neurological deficits (ASIA grade D) with rapid progression (hours to days), (6) current treatment with Bevacizumab and other medication with long half-life that interferes with radiotherapy, (7) life expectancy of less than 3 months, and/or (8) pregnancy.

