Pain response at 2, 4, 6, and 8 weeks and 3 months is defined as [1] a decline in worst pain score of at least two points on an NRS of ten at the treated site without increase in analgesic use or [2] an analgesic decrease of at least 25% without an increase in pain score [25–27]. Worst pain score will be measured with the BPI [15, 16].

Information on duration of the hospital stay in days, days until return to systemic oncological therapy, local control, and progression free survival and overall survival will be captured from the electronic health record. Also, occurrence of neurological deterioration, defined as deterioration of more than one grade on the American Spinal Cord Injury Association (ASIA) scale as measured by physical examination by a neurologists or trained ASIA physician, will be captured from the electronic health record [19, 20].

AEs are defined as any undesirable experience occurring to a patient during the study that may be related to the experimental treatment procedure. AEs during hospital stay will be evaluated using the most recent version of the National Cancer Institute Common Toxicity Criteria of Adverse Events (CTCAE; version 5.0, version 6.0 when available at the start of the study). AEs after hospital discharge reported spontaneously by the patient or observed by the research team will be recorded up to 3 months after treatment.

For cost-effectiveness evaluation, resource use, costs, and quality-adjusted life years (QALYs) are measured for each patient in both randomization groups over the follow-up period. Resource use such as doctor visits, medication, hospital admissions, and surgical interventions, as well as out-of-pocket expenses such as for over-the-counter drugs and travel costs, will be captured using the iMCQ at 3 and 6 months [21]. Where relevant, questionnaire responses will be verified or completed by data from the medical records. Total costs for each patient will be calculated by multiplying the resource use with unit costs. Unit costs will be calculated according to the guidelines for costing research. QALYs will be calculated from the EQ-5D-5L, using the area under the curve approach [23].

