#### Adverse event reporting and harms {22}

Adverse events during hospital stay will be evaluated using the most recent version of the CTCAE (version 5.0, version 6.0 when available at the start of the study). Due to the natural course of the disease, we expect that many patients with spinal metastases suffer from study unrelated AEs. Therefore, only study-related AEs with grade 2 or higher (either expected or unexpected) reported spontaneously by the patient or observed by the research team will be recorded up to three months after treatment.

Grade 3 or higher adverse events are considered serious (S) AEs. (S)AEs that are common in this patient category include urinary tract infections, delirium, pressure sores, and opioid-related adverse drug events and will be recorded but not reported to the ethics committee. Study-related SAEs within 3 months after start of treatment that are life threatening or that resulted in death will be directly reported (within 7 days) to the ethics committee. Other study-related SAEs will be reported to the ethics committee within 15 days. SAEs unrelated to the study will not be directly reported to the ethics committee but documented in the yearly progress report.

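### The neurological deterioration outcome ignores every one-grade ASIA loss, although only patients at grade E or grade D without rapid progression can enter

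*Protocol article*

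**What the plan says.** Outcomes {12} lists the occurrence of neurological deterioration as a secondary outcome, "defined as deterioration of more than one grade on the American Spinal Cord Injury Association (ASIA) scale", judged on physical examination by a neurologist or a physician trained in ASIA grading. Plans for assessment and collection of outcomes {18a} repeats the threshold, "occurrence of neurological deterioration, defined as deterioration of more than one grade", and says that the information comes from the electronic health record.

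Eligibility criteria {10} excludes patients with "neurological deficits (American Spinal Injury Association (ASIA) impairment scale grade A, B, or C) or partial neurological deficits (ASIA grade D) with rapid progression", where rapid means over hours to days.

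Objectives {7} promises a comparison between the arms that includes "neurological deterioration, adverse events (AEs) such as wound complications, HRQOL, and survival between the intervention and control group".

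Adverse events are a separate secondary outcome. Sections {12} and {18a} limit them to experiences that might be related to the experimental procedure. Adverse event reporting and harms {22} adds a further limit on what enters the trial's records, for up to three months after treatment: "only study-related AEs with grade 2 or higher (either expected or unexpected) reported spontaneously by the patient or observed by the research team will be" documented.

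**The concern.** The entry rule and the event threshold do not fit each other. The entry rule removes the three worst grades, and the event threshold then disregards the first step down from each grade that remains. By the protocol's own classification, grade D is a partial neurological deficit and grade C is a deficit that bars entry. A patient without deficit who acquires one (E to D), and a patient who falls from D into an excluded grade (D to C), are both recorded as not having deteriorated.

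What is at stake is the between-arm comparison in Objectives {7}. The spinal cord is the organ at risk that the article singles out when it discusses dose planning (Criteria for discontinuing or modifying allocated interventions {11b}). The safety evidence it cites for the same-day sequence is a study of 13 patients (Provisions for post-trial care {30}). With about 50 patients per arm, an outcome that drops all one-grade losses has little chance of showing a difference in either direction.

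**Working it through.** **The plan's own figures.** The article gives no expected rate, threshold rationale or sample size for this outcome. The only related figure is the sample size for the primary outcome, used here just for the number per arm. With a difference of 13, SD 22, two-sided α of 5% and 80% power, n = 2 × (1.96 + 0.84)² × 22² / 13² ≈ 45 per arm, as stated. The 10% increase gives 50 per arm and 100 in total. Nothing below alters it.

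**Inputs.**
- Event: a fall of more than one grade, that is, at least two ({12}, {18a}).
- Grades that can enter: E, and D without rapid progression ({10}).
- Scale: five grades, A worst to E normal. The article does not spell this out; it is the usual form and fits how {10} uses the grades.

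**Every possible fall from the enrollable grades.**

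| Fall | Grades lost | Event as written | Event if at least one grade |
|---|---|---|---|
| E to D | 1 | no | yes |
| E to C | 2 | yes | yes |
| E to B | 3 | yes | yes |
| E to A | 4 | yes | yes |
| D to C | 1 | no | yes |
| D to B | 2 | yes | yes |
| D to A | 3 | yes | yes |

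Five of the seven types count as written; all seven count with a one-grade threshold. These are types of transition, not numbers of patients.

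**Share of patients missed.** Let q be the proportion of all deteriorations that are exactly one grade. The share missed is q and the share counted is 1 − q. The article gives neither q nor the baseline split between D and E, so a range is all that can be shown: q = 0.5 misses 50%, q = 0.8 misses 80%, q = 0.95 misses 95%.

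**What this does to event counts** (rates of any deterioration are assumed; expected events = 50 × rate × (1 − q)):

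| Assumed rates by arm | Any fall | Counted, q = 0.5 | Counted, q = 0.8 |
|---|---|---|---|
| 10% vs 5% | 5 vs 2.5 | 2.5 vs 1.25 | 1 vs 0.5 |
| 20% vs 10% | 10 vs 5 | 5 vs 2.5 | 2 vs 1 |

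**Whether adverse event recording fills the gap.** Take two patients who each fall from D to C.
- In the intervention arm, after same-day treatment, the fall can be recorded if it is judged related to the procedure. After discharge it must also be grade 2 or higher and be reported or noticed.
- In the control arm, while waiting for radiotherapy, the patient has had no experimental procedure, so the fall lies outside the definition in {12} and {18a}.

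This route therefore picks up one-grade losses unequally and cannot stand in for the comparison by ASIA grade.

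**The case against.** The best defence is that a two-grade threshold trades sensitivity for specificity. Grades are taken from the health record, and clinicians and researchers know the allocation (Who will be blinded {17a}), so small shifts between E and D could be noise or bias. An entry criterion and an event threshold also serve different purposes, so there is no formal contradiction. The definition cites two references that were not available for this review and may support the threshold. This argument has weight for E to D. It is weaker for D to C, which crosses the protocol's own entry boundary. It is also met by reporting both thresholds.

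Two further points stand. The outcome is an unpowered secondary one, and even a full count of one-grade falls would probably be too small for a firm comparison. And recruitment began in November 2022 (Trial status), so the change comes in mid-trial.

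A reader might go further and infer that nearly all clinically important deteriorations go uncounted. The article does not support this. It gives no distribution of grade changes, the most severe falls (E to C or worse, D to B or worse) are counted, and some E to D shifts may be minor. Nor is this the only outcome that could register cord injury. Adverse events judged related to the procedure are recorded separately, and loss of function could show in the physical functioning score.

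**Conclusion.** The concern holds in a limited form. As defined, the outcome misses every one-grade loss from both grades at which patients can enter, including a fall from D into an excluded grade, so it is insensitive in this population. This follows from the two definitions and the eligibility criteria alone, given the usual A to E ordering. The size cannot be computed from the article: the share missed is the unknown share of one-grade falls, 50% if half are one-grade and 80% if four in five are. The event counts shown rest on assumed rates and are only illustrations.

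It may be tempting to add that a near-empty table would be taken as proof of neurological safety. The article states no neurological safety hypothesis (its stated safety hypothesis concerns wound complications), so that is a risk of misreading and not something the plan claims. This is a cheap improvement to a secondary outcome.

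**What to change.** In Outcomes {12} and Plans for assessment and collection of outcomes {18a} together, define neurological deterioration as a worsening of at least one ASIA grade from baseline. Report falls of two or more grades separately by arm, so that the present definition survives as a supplementary count. If at least one grade was intended all along, this simply corrects the wording. Because allocation is not blinded, date and document the change before outcome data are compared between the arms.

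The ASIA grade is already to be drawn from the health record, so no measurement is added. The costs are that some E to D changes due to grading variability will be counted, which the separate reporting makes visible, and that a protocol amendment may be needed. If it is judged substantial under the article's section on amendments {25}, ethics approval and a registry update follow.

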### Participant timeline {13}

**Table Tabb:** 

	Before first consultation with radiation oncologist and orthopedic surgeon	Short after first consultation with radiation oncologist and orthopedic surgeon	Regular PRESENT measurements						
			Baseline	2 weeks	4 weeks	6 weeks	8 weeks	3 months	6 months +

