**Enrolment**									
Informed consent PRESENT cohort	X								
Eligibility screening BLEND RCT	X								
Randomization BLEND RCT	X								
Informed consent BLEND RCT (upon acceptance of intervention)		X							

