#### Implementation {16c}

The research team will screen patients on eligibility. If a patient appears eligible, the research team will perform online randomized allocation.

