### Assignment of interventions: blinding

#### Who will be blinded {17a}

Patients randomized to the control group will not be informed about the trial and receive standard of care. Hence, patients in the control group will be blinded to group allocation. They will even be unaware of the existence of this trial. In contrast, patients randomized to the intervention group will be informed about the intervention which they can accept or refuse. It is not possible to blind researchers and clinicians for group allocation.

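### Randomisation precedes the first specialist consultation and rests on apparent eligibility; with exclusion after randomisation and clinicians who know the arm, removal from the trial can depend on allocation

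*Protocol article*

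**What the plan says.** In the protocol article, the table under Participant timeline {13} has a first column headed "Before first consultation with radiation oncologist and orthopedic surgeon". The rows "Eligibility screening BLEND RCT" and "Randomization BLEND RCT" are both marked in that column. Trial consent and treatment are marked in the next column, shortly after the consultation.

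Implementation {16c} says that the research team screens, and then: "If a patient appears eligible, the research team will perform online randomized allocation".

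Eligibility criteria {10} asks for "spinal instability requiring surgical stabilization (with or without decompression) and radiotherapy". It also asks for fitness for (radio)surgery. It excludes patients in whom SBRT cannot be delivered, those who need more than five levels bridged or radiotherapy at more than one location, those with ASIA grade A to C, and those with grade D progressing over hours to days.

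Criteria for discontinuing or modifying allocated interventions {11b} provides for patients who prove, after randomisation, not to meet the inclusion criteria. They are excluded from the trial. Failed dose planning is given as an example.

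Who will be blinded {17a} states: "It is not possible to blind researchers and clinicians for group allocation". Sections {20a} and {20c} nevertheless specify an intention-to-treat analysis.

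**The concern.** The trial compares two sequences of surgery and radiotherapy in patients who need both. Random allocation makes the arms comparable only for the set of patients who were randomised. If part of that set is removed later, by people who know the arm and on criteria that involve judgement, the analysed arms may differ in prognosis for reasons unrelated to treatment.

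Because the timeline places the first meeting with both specialists after allocation, it is natural that some patients will prove at that meeting not to need surgery, not to be fit for it, or not to be neurologically eligible. Concealment in Castor {16b} protects the sequence only until the code is released. It does not protect decisions made afterwards. The primary outcome is self-reported physical functioning, which is likely to be related to fitness and neurological state, so selective removal on those grounds could move the comparison directly.

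**Working it through.** **Order of events, section by section**

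1. Screening and randomisation come before the first consultation ({13}).
2. Allocation is triggered by apparent eligibility, judged by the research team ({16c}). Trial design {8} and the consent section {26a} instead speak of randomising patients who meet the criteria, so the article is not uniform about how firm eligibility is at allocation.
3. Age, pregnancy, myeloma and earlier treatment of the index level can be read from the record. Surgical indication, fitness, levels to bridge and ASIA grade with its progression normally need clinical assessment. The protocol itself measures ASIA grade by physical examination when it is an outcome ({12}, {18a}).
4. A patient found ineligible after allocation is excluded ({11b}). The dose-planning case is only an example, so the rule also covers indication and fitness. No decision-maker, blinded or otherwise, is named.
5. Clinicians and researchers know the arm ({17a}).
6. The analysis is called intention to treat ({20a}, {20c}). It cannot be so if steps 4 and 5 remove randomised patients.

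**The plan's own figure**

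Inputs from Sample size {14}: difference 13, SD 22, two-sided 5%, power 80%.

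n per arm = 2 × (1.960 + 0.842)² × 22² / 13² = 44.96, so 45. Then 45 / 0.9 = 50 per arm, 100 in total. This reproduces. The 10% allowance names refusal, nonresponse and dropout, not ineligibility.

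**Size, if patients are removed as {11b} says**

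Let f₁ and f₀ be the fractions removed from the intervention and control arms, and g₁ and g₀ the points by which the mean of those removed lies below that of those kept. Then bias = f₁g₁ − f₀g₀. It is zero when removal is the same in both arms and non-zero otherwise. The documents give none of these four quantities.

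The loss of precision can be bounded by assumption. Take equal removal f from 45 evaluable patients per arm:

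power = Φ(13 / (22 × √(2 / (45(1 − f)))) − 1.96)

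| f (assumed) | power |
|---|---|
| 0 | 80.0% |
| 5% | 78.0% |
| 10% | 75.8% |
| 20% | 70.8% |

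**Size, if such patients were kept instead**

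If the effect in them is nil, the expected difference is 13 × (1 − q), where q is the share of such patients. With 45 per arm the standard error is 22 × √(2/45) = 4.64.

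| q (assumed) | difference | power |
|---|---|---|
| 5% | 12.35 | 76% |
| 10% | 11.7 | 71% |
| 20% | 10.4 | 61% |

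This second table does not describe the current plan, which removes these patients. It shows what keeping them would cost, and why few should be left to find after allocation.

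**The case against.** The strongest reply is that the article does not say that eligibility is decided after allocation by the treating specialists. Screening is a separate row that comes before randomisation, patients arrive as referrals and must have radiographic evidence, and a spine surgeon and a radiation oncologist belong to the group overseeing the study {5d}. They may review referral imaging before the visit. That stands. A reader might infer that eligibility as a whole is settled with the arm known, but the documents support only that key criteria may be confirmed, and can be reversed, after allocation.

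The only example in {11b} is failed dose planning, so no reversal of surgical indication is documented. That also stands, but the rule is worded generally.

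A reader might also attach a bias figure by assuming that removals fall on the intervention arm alone. For instance, 20% removed with a 20-point gap gives 0.20 × 20 = 4.0 points. That pattern belongs to failed planning, because control patients have their planning CT only after surgery {11a}. Nothing shows that exclusions arising from the consultation would be one-sided, so the figure should not be used for this point.

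Early allocation also suits the Trials within Cohorts design, since the offer can be made around the visit. This is a convenience. Controls stay uninformed equally well if allocation follows the visit. Finally, neurological deterioration can follow randomisation whenever it takes place, so a later allocation narrows that window but does not close it.

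**Conclusion.** The point holds in limited form. Allocation before the consultation on apparent eligibility, a rule that excludes patients found ineligible afterwards, and clinicians who know the arm together permit allocation-dependent exclusions, contrary to the intention-to-treat analysis that the protocol promises. This rests on one inference: that surgical indication, fitness, levels and neurological grade are normally confirmed only by specialist assessment. If the specialists do confirm them before allocation, the timeline and {16c} should say so.

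The size of the bias is unknown. The loss of power from balanced removal is moderate over the assumed 5% to 20% range. The differences of 12.35 to 10.4 points apply only if ineligible patients are kept. The sample size calculation itself is unaffected. The change is worth making because the sequence is explicit and the correction is cheap.

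**What to change.** 1. In the timeline {13}, move randomisation to directly after the first consultation. Before allocation, the specialists record in Castor that the criteria in {10} are met on the information then available. This should include apparent suitability for SBRT, but not full dose planning, which cannot be required of controls because their planning CT follows surgery. Castor then releases the allocation, and only intervention patients receive the offer.
2. In {16c}, make allocation conditional on confirmed rather than apparent eligibility.
3. In {11b}, state that patients found ineligible after randomisation, for example on failed dose planning, stay in the intention-to-treat analysis, and report their number and reasons by arm.

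The cost is a protocol amendment, a checklist in Castor and an offer made slightly later. The ineligible patients who are kept will dilute the effect slightly, but step 1 should make them few. Recruitment began in November 2022, so for patients already allocated under the present order only step 3 can help. It should be applied to them as well.
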